## 3.8 Justification of the choice of the investigation population

The diagnostic accuracy of the studied procedure could only be evaluated in a comparable patient population, which will be subjected to this imaging modality in the future. An analysis of data from the Swiss Stroke Registry has shown that in other patient populations the frequencies, sizes and distributions of intracranial hemorrhages are considerably different.

Therefore, the investigation population will consist only of patients with symptoms suggestive of a severe life threatening acute ischemic stroke or symptoms suggestive of an intracranial hemorrhage. They will be identified based on clinical symptoms as it is done in clinical practice. Only patients with severe neurological deficits (NIHSS≥7) or symptoms suggestive of an intracranial hemorrhage are eligible. These criteria were chosen as in clinical practice these patients are most likely to be triaged with a direct to angiography approach.^11, 12^

Consequently, this investigation will include mainly vulnerable patients. As specified by the inclusion criteria, only patients with severe neurological deficits (NIHSS ≥7) or symptoms suggestive of an intracranial hemorrhage (for example reduced level of consciousness) are eligible. Some of these patients may not be able to give informed consent. Furthermore, the underlying disease may require emergency treatment including immediate therapeutic decisions under life threatening time pressure. There is no alternative group of patients capable of judgement, with the same life-threatening condition and with such a severe deficit in whom this diagnostic procedure could be studied and where inclusion in such a trial could be justified. Because we include mainly vulnerable patients in an emergency situation and due to the life-threatening situation, no delay to the enrolment procedure can be risked. We will obtain informed consent from the patient if he/she is capable of giving informed consent. The enrolling physician will decide after consultation with the treating neurologist if the patient is able to give informed consent. If he/she is not able to give informed consent due to the severity of his/her neurological deficit, the patient will be included in the trial without prior informed consent by him-/herself or a next of kin/LAR and recovery consent from the patients or his/her next of kin/LAR has to be obtained post-hoc. An independent physician will be consulted prior to enrolling the patient into the trial to ensure and confirm that the enrollment of the patient is in his/her best interest. Each institution must follow their institutional and national EC policy as well as local IRB policy (if applicable) for obtaining informed consent. For details about patient information and informed consent see section 2.7.

# 4. CLINICAL INVESTIGATION OBJECTIVES

## 4.1 Overall Objective

The overall objective is to evaluate the diagnostic ability of the non-contrast syngo DynaCT Sine Spin for the detection of intracranial hemorrhages.

## 4.2 Primary Objective

The primary Objective is to evaluate if non-contrast syngo DynaCT Sine Spin imaging is non-inferior for the detection of intracranial hemorrhages compared to non-contrast MDCT imaging. It will be deemed non-inferior if the lower bound of the 95%-CI of the sensitivity is above 95% and the lower bound of the 95%-CI of the specificity is above 95% for the detection of intracranial hemorrhages (pre-defined non-inferiority margin).

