| Measurements and procedures: | All subjects will undergo non-contrast cranial MDCT and non-contrast FDCT imaging with a maximal time span of four hours between the two scans. Only patients in whom no invasive procedure is planned or performed in between the scans can be enrolled. Subjects will be enrolled based on clinical features (symptoms of the stroke) and according to a pre-defined number of needed hemorrhagic and non-hemorrhagic stroke patients. They will be recruited in a ratio of 1:1. This will be secured over an online enrollment system in which the investigator has to enter if a patient has a hemorrhagic (and location of hemorrhage) or non-hemorrhagic stroke. All sites must maintain screening logs.  To ensure compliance with the Protocol and adequate acquisition technique of the FDCT and MDCT at the respective site the first five cases from each site will be deemed as lead-in cases. Cases can be excluded and deemed as Screen Failures if they show clear evidence of (a) operator failure (for example due to clear artifacts due to objects in the field of view, wrong positioning of head, wrong acquisition protocol, severe motion artifacts, missing reconstructions) or (b) technical failure due to missing calibration of the scanner. The ultimate decision to exclude cases is made by the Independent Core Lab (under the supervision of [name]). In such a case it is the obligation of the Sponsor to perform retraining. Excluded cases will be replaced to ensure adequate power.  All non-contrast MDCT and FDCT scans will be rated by blinded readers, who were not involved in the original treatment or enrollment of the subjects on an individual basis in a core-lab (the core lab service will be provided by the Neurovascular Imaging Research Core, [name], University of California Los Angeles, Los Angeles, USA). The readers will be experienced in neuroimaging. All scans will be reconstructed in a standardized matter (i.e., fixed slice thickness 5 mm, distance 3 mm and angles – orbitomeatal) and randomized prior to evaluation. All MDCT scans will be read by one reader with no time-limit, while all FDCT scans will be read by six readers with a time-limit of 90 seconds (only applicable to the decision hemorrhage positive or negative). The reader of the MDCT scan will not be part of the six readers who read the FDCT scans. Each of the six readers will read all FDCT scans completely independent from the other readers, and they will not share any information.  The ground truth (i.e., if an intracranial hemorrhage is present) will be defined based on the MDCT readings according to the following procedure. If the readings of the clinical reader and the core-lab are consistent, this will be deemed as ground truth. In case they are inconsistent (i.e., at the clinic it is rated as hemorrhage positive and in the core-lab as hemorrhage negative or vice versa) a second independent core-lab consisting of a highly experienced neuroradiologist ([name], Inselspital Bern, Bern, Switzerland) will read the MDCT scan and review all available clinical data. Based on this information he will make a final ruling (i.e., define the ground truth for this patient, majority vote).  The FDCT readings of the six Core-Lab readers will be compared with the ground truth and based on this comparison they will be rated as true positive, true negative, false positive or false negative. These values will be calculated for each reader separately. In case most of the core-lab 1 readers (at least 5 out of 6) detects a hemorrhage on the FDCT scan, which according to the ground truth was hemorrhage negative the second core-lab will use all available clinical data to deduce if there is any evidence for the hemorrhage to have occurred between both scans. In this case the patient will be excluded from further analysis.  See table 1 for a detailed overview of all possible constellations.   \| Ground truth \| Core-Lab 1 \| Core-Lab 2 \| Final Result \| \| --- \| --- \| --- \| --- \| \|  \| FDCT \| Unblinded \| FDCT \| \| (+) \| (+) \| NA \| True (+) \| \| (-) \| (-) \| NA \| True (-) \| \| (+) \| (-) \| NA \| False (-) \| \| (-) \| (+) \| (-) \| False (+) \| \| (-) \| (+) \| (+) \| Hemorrhage occurred between scans \|   Table 1. Overview of possible outcomes  The results are used to calculate the sensitivity and specificity of the FDCT. |

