However, the widespread implementation of this direct to angiography workflow has been impended by the difficulty of differentiating between ischemic and hemorrhagic stroke with FDCT.^39, 40^ As it is not possible to differentiate between ischemic and hemorrhagic stroke without brain imaging, it is of pivotal importance that hemorrhage exclusion can be performed safely and reliably with native FDCT imaging as well. A missed intracranial hemorrhage, i.e. an hemorrhagic stroke (which make up between 15 and 20% of all severely affected stroke patients according to an analysis of the Swiss Stroke Registry) could have potentially dramatical (and lethal) consequences due to different treatment strategies.^41^ Up till now this was only evaluated in retrospective studies, which showed very high sensitivity and specificity in the detection of intracranial hemorrhage with the last generation of FDCT.^6, 18^ However, prospective high-quality studies with large patient cohorts on this topic are still missing. We further did not find any ongoing studies on clinicaltrials.gov or within the WHO trial registry.

Therefore, we aim with this study to investigate if non-contrast syngo DynaCT Sine Spin imaging is non-inferior to non-contrast MDCT imaging regarding its sensitivity and specificity for the detection of intracranial hemorrhages. Non-contrast syngo DynaCT Sine Spin imaging will be deemed non-inferior if the lower bound of the 95%-confidence interval (95%-CI) of the sensitivity is above 95% and the lower bound of the 95%-CI of the specificity is above 95% (pre-defined non-inferiority margin). If non-inferiority could be established, this would guarantee for a safe triage of stroke patients. We are confident, that if our study shows non-inferiority of non-contrast syngo DynaCT Sine Spin imaging it will pave the way for the widespread implementation of the above described direct to angiography workflow, allowing more AIS patients to live a self-sustained, independent life after their stroke. Due to the high burden of disease any measurement of improvement is of high need. Conversely if our study fails to establish non-inferiority of non-contrast syngo DynaCT Sine Spin imaging for the detection of intracranial hemorrhage, it might prevent patients from undergoing harmful treatments.

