## 3.6 Explanation for choice of comparator/ground truth

To calculate the sensitivity and specificity of non-contrast syngo DynaCT Sine Spin imaging a ground truth must be defined. The ground truth will be defined based on the MDCT images from the same patient. MDCT was chosen as the reference standard for the following reasons:

(1) It is standard of care in most hospitals worldwide for the detection of intracranial hemorrhages in acute stroke patients.^19, 44^

(2) It was identified as the gold standard for the detection of intracranial hemorrhages by the American Heart Association/American Stroke Association (AHA/ASA).^19, 44^

(3) It has very high sensitivities for the detection of intracranial hemorrhages. Recent studies yielded sensitives of 99.7% to 100% for the detection of subarachnoid hemorrhages (SAHs), even in non-academic centers.^45-47^

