## 6.2 Methods for minimizing bias

The components of the primary endpoint “occurrence of an intracranial hemorrhage” will be assessed by independent readers blinded to all clinical information. They will not be involved in the enrollment or treatment of any patient and will have no information on the distribution of patients (i.e. the number of patients with hemorrhage or without hemorrhage).

For this purpose, all scans will be reconstructed in a standardized manner first by the coordinating center to guarantee comparability between all scans. Fixed slice sizes and angels will be used for all scans. After reconstruction all scans will be pseudonymized and randomized. The order of the scans will differ for each rater. Furthermore, a time limit of 90 seconds will be used for the evaluation of the FDCT scans (only applicable to the binary decision hemorrhage yes/no) to ensure comparability to real-life conditions. No time-limit will be set for the MDCT scans as these are set as ground truth and therefore their diagnostic power will not be benchmarked.

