## 11.1 Hypothesis

Null hypothesis: Sensitivity and specificity of non-contrast contrast syngo DynaCT Sine Spin to detect the presence (sensitivity) and absence (specificity) of intracranial hemorrhages are inferior to MDCT. Inferiority is given when one of the lower bounds of the 95%-CI of sensitivity and specificity are equal or lower than 95%.

Alternative hypothesis: Sensitivity and specificity of non-contrast contrast syngo DynaCT Sine Spin to detect the presence (sensitivity) and absence (specificity) of intracranial hemorrhages are non-inferior to MDCT. Non-inferiority is given when both lower bounds of the 95%-CI of sensitivity and specificity are higher than 95%.

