### 11.5.2 Primary Analysis

The primary analysis will be based on the FAS. As described for the sample size calculation, a generalized linear random-effects model with a logit link function will be fit. The explanatory variables ’reader’ and ’patients’ will be random effects. Difficult cases will be weighted with 2%. From the fixed-effect intercept of sensitivity and specificity, the 95%-CIs will be calculated applying the method of Wald. Sensitivity will be calculated based on the results of all core-lab readers of the non-contrast syngo DynaCT Sine Spin scans of all patients for which the ground truth was deemed to be hemorrhage positive. Specificity will be calculated based on the results of all core-lab readers of the non-contrast syngo DynaCT Sine Spin scans of all patients for which the ground truth was deemed to be hemorrhage negative. It will be tested whether both the lower bound of the 95%-CI of the sensitivity and specificity are higher than the margin of 95%.

All results will be reported in concordance with the STARD guidelines.^20^

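### The primary claim is non-inferiority of FDCT to MDCT, but the rule tests FDCT against a fixed 95% goal with MDCT as the reference, so it supports a performance claim rather than a comparative one

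*Protocol*

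**What the plan says.** The comparative framing runs through the protocol. The title calls the study a non-inferiority comparison of FDCT to MDCT. Section 3.1 asks whether FDCT is "non-inferior to non-contrast MDCT imaging regarding its sensitivity and specificity", section 4.2 aims to "evaluate if non-contrast syngo DynaCT Sine Spin imaging is non-inferior for the detection of intracranial hemorrhages compared to non-contrast MDCT imaging", and both hypotheses in 11.1 are worded relative to MDCT.

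The criterion attached to that framing concerns FDCT alone. Section 11.1: "Non-inferiority is given when both lower bounds of the 95%-CI of sensitivity and specificity are higher than 95" per cent. Section 11.5.2: "It will be tested whether both the lower bound of the 95%-CI of the sensitivity and specificity are higher than the margin of 95" per cent. Section 6.1 says the thresholds came from expert statements.

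MDCT supplies the truth. Section 3.6: "The ground truth will be defined based on the MDCT images from the same patient". Under 6.1, truth is the MDCT reading on which the clinical and core-lab readers agree. If they disagree, a second core lab rules and may use clinical information. Section 6.2 says of the MDCT scans that "these are set as ground truth and therefore their diagnostic power will not be benchmarked".

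Reading conditions differ. Synopsis: "All MDCT scans will be read by one reader with no time-limit, while all FDCT scans will be read by six readers", the latter with 90 seconds for the yes/no decision and blind to clinical data.

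**The concern.** A non-inferiority comparison of two diagnostic modalities needs the accuracy of both against a common truth, and a margin on their difference or ratio. Here one modality is the source of the truth, its accuracy is not estimated, and no difference is defined. The 95% is called a non-inferiority margin but works as an absolute performance goal.

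What is at stake is the permitted conclusion. Section 3.1 already plans strong readings of both results: success is to secure safe triage, and failure is to protect patients from harmful treatment. Section 12.5 lets the funder use the data in regulatory applications and, with approval for selected images, in marketing. A claim of non-inferiority to MDCT would say more than was measured. A failed result would invite the reading that FDCT is worse than MDCT, although MDCT was never read by six blinded readers against the clock.

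**Working it through.** **1. What is tested.** Write Se and Sp for sensitivity and specificity.

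- Comparative null implied by the label: Se(MDCT) − Se(FDCT) ≥ δ, or the same for Sp, for a stated δ, both measured against a common truth.
- Null implied by the rule in 4.2, 11.1 and 11.5.2: Se(FDCT) ≤ 0.95 or Sp(FDCT) ≤ 0.95, with truth = adjudicated MDCT.

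The second contains neither an MDCT parameter nor δ.

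**2. The plan's own sample size.** Inputs in 11.2: FDCT sensitivity 99% (readers 98.5%, 99%, 99.5%), FDCT specificity 98% (97.5%, 98%, 98.5%), 70% sensitivity in 14 difficult cases with total weight 2%, six readers, 90% power, margin 95%, drop-out 5%. The stated total reproduces from 238 evaluable patients: 238/2 = 119 per group; 119/0.95 = 125.3, rounded up to 126; 2 × 126 = 252. The 238 comes from a simulation with a reader correlation called high but given no value, so it cannot be reproduced exactly. That does not matter here: no input is an MDCT accuracy or an FDCT–MDCT difference. The size was computed for the fixed 95% test.

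**3. When the rule amounts to a comparison.** If true MDCT accuracy is r, a 95% floor on FDCT corresponds to a margin of r − 0.95:

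| r | implied margin |
|---|---|
| 100% | 5 points |
| 99.7% | 4.7 points |
| 99% | 4 points |
| 98% | 3 points |

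The 99.7% is the lower end of the sensitivity range for subarachnoid haemorrhage in 3.6; 99% and 98% are assumptions. Section 3.6 gives no MDCT specificity and no figure for other bleeding types. By 3.7, subarachnoid haemorrhage is expected in 5–10% of subjects and intraparenchymal or intraventricular haemorrhage in about 40–45%.

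**4. What reference error does.** With half the patients bleeding, a reference with Se = Sp = r, and errors independent given the true state:

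apparent Se(FDCT) = [0.5·Se·r + 0.5·(1 − Sp)(1 − r)] / [0.5·r + 0.5·(1 − r)] = Se·r + (1 − Sp)(1 − r), and likewise for Sp.

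- A flawless FDCT (Se = Sp = 1) shows exactly r: 0.997, 0.99 or 0.98.
- At the plan's 99% and 98%, r = 0.99 gives 0.99 × 0.99 + 0.02 × 0.01 = 0.9803 for sensitivity and 0.98 × 0.99 + 0.01 × 0.01 = 0.9703 for specificity.

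Independent reference error is therefore charged to FDCT. If both modalities miss the same bleeds, the shared error counts as agreement and flatters FDCT. The design cannot separate the two.

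**5. The outcome table.** In Table 2 of section 6.1, a negative FDCT with positive truth is always a false negative. A positive FDCT with negative truth is either a false positive or a bleed that arose between the scans. No row covers a bleed that MDCT missed, even where at least five of six FDCT readers see it.

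**6. What a real comparison would need.** For a paired comparison against an independent reference, with margin 0.05, one-sided 2.5%, 90% power, one reader per modality and independent errors:

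n = (1.96 + 1.2816)² × (p10 + p01 − d²) / (0.05 − d)²,

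where p10 and p01 are the two discordant proportions and d the MDCT-minus-FDCT difference.

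- Sensitivity, FDCT 99%: 66 truth-positive patients if MDCT is 100%, 84 if 99%.
- Specificity, FDCT 98%: 229 truth-negative patients if MDCT is 100%, 165 if 98%.

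The plan has 119 evaluable per group; six readers would change these sizes. All MDCT rates here are assumptions, because the protocol gives none against an independent reference.

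**The case against.** The strongest reply is that nothing is hidden. The synopsis defines the criterion with MDCT as the reference standard, 3.6 gives reasons for that choice, and 6.1 argues that comparison with the gold standard is the only way to benchmark FDCT. The overall objective (4.1) and the outcome (5.1) concern FDCT's own diagnostic performance. If MDCT is accepted as error-free, the rule is non-inferiority with a 5-point margin. All of this stands, and it limits the point to wording and inference. It does not supply the missing comparison: the equivalence is conditional on an assumption that 3.6 supports only in part.

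The 90-second limit is deliberate and explained. It handicaps FDCT, so it does not make a false pass easier. What remains is that a failure could reflect time pressure and blinding rather than the modality.

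Two stronger readings are tempting and should not be made.

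- A reader might infer that MDCT is perfect by construction. Only concordant MDCT readings are correct by definition. Where the clinical and core-lab readings disagree, the second core lab rules, so an individual MDCT reading can be overruled.
- A reader might infer that an FDCT equal to MDCT at, say, 97% would be bound to fail, since the Wilson lower limit for 115 of 119 single readings is about 0.917. The plan does not use that limit. It uses six readers and a Wald limit on a mixed-model intercept, which sits above the raw rate. In simulations of the planned type of analysis at a raw 97%, the 95% rule was met in about 87%, 99%, 87% and 56% of runs at assumed reader correlations of 0.1, 0.2, 0.5 and 0.8. The true correlation is not stated, so no certain failure can be claimed.

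**Conclusion.** The point holds as a mismatch between the claim and the test. The label in the title, synopsis, 3.1, 4.2 and 11.1 is comparative; the rule is a fixed 95% performance goal for FDCT against adjudicated MDCT. Passing shows agreement with that reference beyond 95% on both measures. It becomes non-inferiority to MDCT, with a margin of 5 points, only if the MDCT-based truth is taken as error-free; the implied margin is 3 to 4.7 points if true MDCT accuracy lies between 98% (assumed) and 99.7%. Failing does not show that FDCT is worse than MDCT read under the same conditions.

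The sample size, the error level and the decision rule are not at fault on this point: they are consistent with one another and with a performance goal. The change should be made because it alters what the trial may conclude.

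**What to change.** Restate the primary objective (synopsis and 4.2), the hypotheses (11.1) and the planned conclusion along these lines: FDCT meets a pre-set performance goal if the lower 95% limits of sensitivity and specificity, with adjudicated MDCT as reference standard, both exceed 95%. Carry the same wording into 3.1 and, where practicable, the title. Do not conclude that FDCT is non-inferior to MDCT.

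Optionally, tabulate from readings already planned how often the clinical and core-lab MDCT readings disagreed and which way the second core lab ruled. This gives context on MDCT reading variation but does not estimate MDCT accuracy, since errors shared by both readers stay unseen.

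The cost is a wording amendment and, if wanted, one table. The decision rule, 252 patients and six readers are unchanged; the downside is a less attractive claim. Keeping the comparative claim would instead need an independent reference, MDCT accuracy measured against it, and a margin on the difference.

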## 4.3 Secondary Objectives

The secondary Objectives are to determine:

- the positive predictive value of FDCT for the detection of intracranial hemorrhages.
- the negative predictive value of FDCT for the detection of intracranial hemorrhages.
- the interrater agreement of FDCT with regard to the occurrence of intracranial hemorrhage

